## 3. Discussion

To our knowledge, this is the first study to investigate the synergy effect of combination of Xuesaitong and aspirin. Aspirin is widely used in clinical practice for primary and secondary prevention of cardiovascular and thrombotic cerebrovascular events [1, 2, 19]. However, the use of aspirin is well recognized to be associated with the risk of some gastrointestinal complications [20, 21]. With the aging of society, the use of aspirin has continued to increase, and the gastrointestinal injury induced by aspirin, even at low doses, has become a clinical problem that needs attention. Some key strategies have been proposed to minimize the aspirin-induced gastrointestinal injury, such as reducing the dose or frequency of aspirin administration, concomitant use of a gastroprotective drug, or even stopping administration of aspirin [22]. But these therapeutic regimens still remain in a dilemma between the prevention of thrombotic diseases and serious gastrointestinal complications. In order to solve this issue, it is urgent to find and establish therapeutic scheme that can not only effectively guarantee the clinical efficacy of aspirin but also prevent gastrointestinal injury. Since the dual-directional regulation of Xuesaitong, it became the potential combination of aspirin to solve the clinical dilemma above.

Xuesaitong, a marketed Chinese medicine with the main active component of PNS, has been widely and long-term used to prevent and treat hematological diseases and cardiovascular diseases [23]. Several clinic trials indicated that Xuesaitong could inhibit platelet activation in patients with blood hyperviscosity syndrome [24]. Interestingly, as for the widespread clinical application together with aspirin, many clinicians found its ability to protect against gastrointestinal injury. In view of this protective efficacy, some researches have shown that Xuesaitong could enhance the proliferative ability of human endothelial cells to heal the wound and stop bleeding [25]. Our previous studies demonstrated Xuesaitong can alleviate gastrointestinal injury caused by aspirin in rats [13]. Combined with HE staining results, our results indicate that the protective mechanism of Xuesaitong on aspirin-induced gastrointestinal injury may act through increasing VEGFA and protecting gastrointestinal mucosa. As for Xuesaitong's ability that both effectively guarantee the clinical efficacy of aspirin and prevent gastrointestinal injury, it is worthwhile to further study the mechanism of the combination of these two drugs and supply a rational combination. Since we have proved that aspirin and Xuesaitong could increase the AUC of each other [11, 12], this means the content of effective drugs in the blood increased. In order to achieve the same blood concentration, the intake of aspirin might be reduced, the adverse reaction might also reduce accordingly. To explore the possibility of reducing the dose of aspirin, it is worth making clear the efficacy and safety of the combination of aspirin and Xuesaitong. By using this randomized controlled noninferiority trial, determining the clinical efficacy indexes like aggregation rate, platelet membrane glycoprotein indexes, and gastrointestinal injury indexes like calcitonin activity and I-FABP allows us to find out whether the platelet aggregation in patients was excessively inhibited and whether the digestive tract injury caused by aspirin is alleviated under drug combination.

In conclusion, the results of this study are expected to provide evidence of high methodological quality on the synergy effect of combination of Xuesaitong and aspirin for CHD synergy effect of combination of Xuesaitong and aspirin.

## Figures and Tables

**Figure 1 fig1:**
[figure not shown]
A schematic flowchart of the clinical trial.

**Table 1 tab1:** Flowchart of a patient follow-up

Group	Screening D-7 to D1	D1	D30	D31 closeout
Patient information	X			
Physical examination	X	X		X
Vital signs	X			X
Blood routine; serum biochemistry; urine routine; stool routine; coagulation routine	X^1^	X^1^		X^1^
ECG	X			X
Stool biomarkers (calprotectin; I-FABP)		X	X	
Blood biomarkers (platelet aggregation; P2Y12; PAC-1; P-selectin)		X	X	

D: day; ECG: electrocardiogram; I-FABP: intestinal fatty acid-binding protein; PAC-1: platelet-associated complement 1. ^1^If the abnormality of this program is clinically significant, if it occurs before screening and at baseline, the subjects will be excluded directly. If it occurs during the observation period of administration, the retest will be followed up until the examination is normal or the abnormality is considered by the study doctor to be of no clinical significance.

**Table 2 tab2:** Inclusion, exclusion, and termination criteria.

Criteria
*Inclusion criteria*
(1) 45–75 years of age without gender restriction
(2) Meet the diagnostic criteria of CHD
(3) Meet the diagnostic criteria of grade I–II angina
(4) Meet the diagnostic criteria of blood stasis
(5) Meet the diagnostic criteria of stable angina pectoris
(6) Take regular aspirin (enteric-coated) for at least one year (the incidence of bleeding events, adverse events (AEs), and adverse reactions will be noted)
(7) Calprotectin in stool is above 50* μ*g/g
(8) Before the study start, patients and their families are fully informed and voluntarily willing to sign an informed consent

*Exclusion criteria*
(1) Mental or physical disorders
(2) Pregnant, menstruating, and breastfeeding women
(3) Severe heart disease and severe cardiopulmonary dysfunction
(4) Severe primary diseases, such as cancer, liver and renal damage, and multiple organ failure
(5) Poorly controlled hypertension (>160/100 mmHg)
(6) Current participation in another clinical trial or participation in another clinical trial within three months
(7) Having underwent surgery within eight weeks
(8) Having drug allergy history or allergic constitution
(9) Diabetes
(10) Status epilepticus
(11) Unstable vital signs
(12) Combined with serious infection, infectious diseases
(13) Acute intestinal infection
(14) Unsuitability or poor compliance for this trial

*Termination criteria*
Participant termination
(1) Serious adverse events occur or having obvious abnormal value of the laboratory tests
(2) The investigators believe someone's trial needs to be terminated because of medical, safety, or GCP considerations
Trial termination
(1) Half of the participants have mild adverse events other than gastrointestinal reactions
(2) The investigators believe it is necessary to abort the trial for medical or safety purposes

**Table 3 tab3:** Dose and duration of medication.

Group	Medication	Dose and method	Duration
Aspirin group	Enteric-coated aspirin	100 mg, q.d., oral	30 days
Xuesaitong group	Xuesaitong soft capsule	200 mg, t.i.d., oral	30 days
Drug combination group	Xuesaitong soft capsule + enteric-coated aspirin	100 mg q.d. oral aspirin and 200 mg t.i.d. oral Xuesaitong soft capsule	30 days

**Table 4 tab4:** Clinical outcomes of the trial.

Items
*Primary outcomes*
Primary outcomes of improving efficacy
Platelet aggregation rate (platelet aggregation analyzer)
Primary outcomes of reducing gastrointestinal side effects
Change in calprotectin activity (ELISA) [17]

*Secondary outcomes*
Secondary outcomes of improving efficacy
(1) Change in PAC-1 activity (flow cytometry)
(2) Change in P-selectin activity (flow cytometry)
(3) Change in P2Y12 acceptor activity (flow cytometry)
Secondary outcomes of reducing gastrointestinal side effects
(1) Change in I-FABP activity (ELISA) [18]
(2) Change in fecal occult blood

*Safety outcomes*
(1) Serum biochemistry
(2) Blood routine
(3) Urine routine
(4) Stool routine
(5) ECG

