**Methods:**

This trial is a prospectively planned, open-labeled, parallel-grouped, single-centered clinical trial. A total of eligible 480 participants will be randomly allocated into three groups: aspirin group, Xuesaitong group, and drug combination group at a ratio of 1 : 1 : 1. The primary outcome is the change of platelet aggregation rate and calprotectin activity. Secondary outcomes include PAC-1, P-selectin, P2Y12, I-FABP activity, and fecal occult blood. *Discussion*. The results of the study are expected to provide evidence of high methodological and reporting quality on the synergy function of Xuesaitong and aspirin upon the antiplatelet and anti-gastrointestinal injury effect for CHD. It also provides an experimental basis for clinical rational drug combination therapy. *Trial Registration*. This trial was registered in the Chinese Clinical Trail Registry, ChiCTR2000036311, on 22 August 2020, http://www.chictr.org.cn/edit.aspx?pid=58798&htm=4.

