Xuesaitong capsule is a marketed Chinese medicine with components of Panax notoginseng saponins (PNS), which is a mixture of ginsenosides Rb1, Rg1, Rd, Re, and notoginsenoside R1. It has been used in combination with aspirin in preventing cardiovascular disease for several years with a good clinical effect [7, 8]. Our previous study has indicated that the combination could inhibit platelet activation caused by blood hypercoagulability and reduce platelet aggregation to prevent thrombosis [9, 10]. These effects may rely on another finding from our team, which shows that aspirin and Xuesaitong could increase the area under the curve (AUC) and promote the absorption of each other [11, 12]. More interestingly, our research also found Xuesaitong attenuates expression of aspirin-induced tight junction protein and apoptosis of crypt epithelial cells in small intestine [13]. It means Xuesaitong may serve as a pharmacological treatment for aspirin-induced gastrointestinal injury. Since the dual-directional regulation of Xuesaitong, it became the potential combination therapy to solve the clinical dilemma. All the preclinical evidences have elucidated the combination could enhance aspirin's efficacy and decrease aspirin-induced gastrointestinal injury. However, it still lacks high-level clinical evidence.

In this study, we conducted a randomized controlled noninferiority trial to explore whether the efficacy and safety of combination for CHD patients are superior to the single use.

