## 2. Methods

### 2.1. Study Design and Setting

This is a prospectively planned, open-labeled, parallel-grouped, single-centered clinical trial. The trial will be conducted at the outpatient care of the Cardiology Department at the Dongzhimen Hospital, Beijing University of Chinese Medicine in China. The staff of the department will be informed of the trial and they will help researchers to recruit participants. The trial is conducted by the ethical principles laid down in the Declaration of Helsinki, the Guideline for Good Clinical Practice, and local laws. The informed consent form will be obtained from all participants before any trial-related procedures were conducted, enrolled after a complete and extensive description of the study. The trial was approved by the Ethics Committee of Dongzhimen Hospital, Beijing University of Chinese Medicine (Supplementary File 1). We present the protocol in accordance with the SPIRIT reporting checklist (Standard Protocol Items Recommendations for Interventional Trials) (Supplementary File 2).

In terms of research methods, we refer to and improve one of our previous experimental designs [14]. 480 participants will be randomly assigned to either an aspirin group, a Xuesaitong group, or drug combination group at a ratio of 1: 1: 1. Participants in the aspirin group will be administered aspirin (100 mg, qd) orally 30 min after breakfast, participants in the Xuesaitong group will be administered Xuesaitong soft capsule (contains PNS and excipients; 200 mg, tid) orally 30 min after breakfast, and participants in the drug combination group will be administered both drugs above. The two drugs should be taken half an hour apart, and aspirin should be taken first. All treatment courses will last for 30 days. Blood samples will be acquired 30 min before administration on day 1 and 30 min after administration on day 30. The volume of each blood sample is 4 mL. And fecal samples will be collected on days 1 and 30. Details of patient follow-up are summarized in Table 1 and Figure 1.

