### 2.6. Combination

Participants are not allowed to take any kind of herbal or chemical medication which have the pharmacological effects of activating blood circulation, preventing platelet aggregation, or anti-inflammatory activityParticipants with angina pectoris could take isosorbide mononitrate. In addition, participants could take other medications that have no known drug-drug interaction with aspirin or Xuesaitong soft capsule

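### All participants are established aspirin users, so for calprotectin the Xuesaitong arm is a switch from aspirin, and superiority of the combination over it is not to be expected

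*Protocol article*

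**What the plan says.** **Who enters.** Table 2 of the protocol article, inclusion criterion (6), requires that patients "Take regular aspirin (enteric-coated) for at least one year". Criterion (7) adds "Calprotectin in stool is above" 50 µg/g. Both apply to all three arms.

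**What they receive.** Section 2.1 and Table 3 give aspirin alone to one arm. For the others, "participants in the Xuesaitong group will be administered Xuesaitong soft capsule" and "participants in the drug combination group will be administered both drugs above", for 30 days. On other medication, section 2.6 says "Participants are not allowed to take any kind of herbal or chemical medication which have the pharmacological effects of activating blood circulation"; the same sentence goes on to cover drugs against platelet aggregation. Non-study aspirin therefore cannot continue in the Xuesaitong arm.

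**What is measured.** The Abstract says "The primary outcome is the change of platelet aggregation rate and calprotectin activity". Table 4 places calprotectin under the reduction of gastrointestinal side effects. Stool is collected on days 1 and 30.

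**What is claimed.** The Introduction sets out to "explore whether the efficacy and safety of combination for CHD patients are superior to the single use". The Discussion puts a narrower gastrointestinal question: whether giving both drugs relieves the digestive-tract injury that aspirin causes. Section 2.10 plans comparisons between treatment groups without naming a pair.

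**The concern.** The arms are presented as two monotherapies and a combination. In this population they amount to continuing aspirin, switching from aspirin to Xuesaitong, and adding Xuesaitong to aspirin. On calprotectin, the combination differs from the Xuesaitong arm only by aspirin, which the protocol names as the cause of the injury. Full protection would bring the combination level with an arm no longer exposed to aspirin, not below it.

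Two errors could follow. If single use is read as both single drugs, a combination that works as hoped against aspirin injury could still be reported as not superior, or even as worse. Conversely, lower calprotectin on Xuesaitong than on aspirin could be credited to Xuesaitong when part or all of it comes from stopping aspirin. No arm separates the two.

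**Working it through.** **The plan's own figure.** Section 2.4 gives 131 per arm, but for platelet aggregation (38.72% versus 37.79%). No SD or margin is stated, so 131 cannot be reproduced; treated as a difference of means, 0.93 points would need an SD of about 2.69 (two-sided 0.05, 80% power). No figure is given for calprotectin. I use 131 below only as a number per arm.

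**Inputs.** From the documents: 131 per arm (section 2.4), 160 per arm enrolled (480/3), two-sided 0.05 (section 2.10). Assumed, because the documents give no value:
- A: calprotectin excess due to continued aspirin at day 30, in SD units, 0.3 to 0.8
- f: share of aspirin injury that Xuesaitong removes, 0 to 1, the same in both arms that receive it
- r: share of A that resolves by day 30 after stopping aspirin, 0 to 1
- b: calprotectin not due to aspirin; d: any Xuesaitong effect on b

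**Step 1, expected day-30 level.**
- Aspirin: b + A
- Combination: b - d + (1-f)A
- Xuesaitong: b - d + (1-r)(1-f)A

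**Step 2, differences.**
- Combination minus Xuesaitong: (1-f)A - (1-r)(1-f)A = r(1-f)A, at least 0 for every r and f between 0 and 1
- Combination minus aspirin: -fA - d
- Xuesaitong minus aspirin: -d - (r + f - rf)A. With an inert Xuesaitong (f = 0, d = 0) this is -rA, which is withdrawal alone.

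**Step 3, size.** Normal approximation, d = 0, SE = √(2/131) = 0.1236 SD. For a true difference δ in a given direction, the chance of a significant result in that direction is Φ(δ/SE - 1.96), and in the opposite direction Φ(-δ/SE - 1.96).

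| A | f | r | Combination minus Xuesaitong | Combination significantly lower than Xuesaitong | Combination significantly higher than Xuesaitong | Combination significantly lower than aspirin |
|---|---|---|---|---|---|---|
| 0.5 | 1 | any | 0 | 2.5% | 2.5% | 98.2% |
| 0.5 | 0.5 | 1 | 0.25 | <0.01% | 52.5% | 52.5% |
| 0.5 | 0.5 | 0.5 | 0.125 | 0.15% | 17.1% | 52.5% |
| 0.3 | 0.5 | 1 | 0.15 | 0.08% | 22.8% | 22.8% |
| 0.8 | 0.5 | 1 | 0.40 | <0.01% | 89.9% | 89.9% |

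Example, second row: 1 × 0.5 × 0.5 = 0.25; 0.25/0.1236 = 2.02; Φ(2.02 - 1.96) = 52.5%. With 160 per arm this becomes 60.9%. At f = 1 the difference is 0, so the 2.5% does not depend on sample size.

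**Step 4, the reverse error.** With A = 0.5 and an inert Xuesaitong, the Xuesaitong arm would still be significantly lower than aspirin with probability 98.2% if r = 1 (δ = 0.5) and 52.5% if r = 0.5 (δ = 0.25).

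**The case against.** **Slow recovery.** After a year or more on aspirin, injury may not clear in 30 days. If Xuesaitong acted on injury from ongoing aspirin but not on what remains after stopping, the difference would be (r-f)A, which favours the combination when r < f (for example -0.5A at r = 0.5, f = 1). That requires Xuesaitong to treat the same injury in one arm and not in the other, and the protocol says nothing to suggest it. With a common f the result is r(1-f)A and needs no assumption of full recovery.

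**Mutual absorption.** The Introduction and Discussion say each drug raises the other's AUC, so Xuesaitong exposure may be higher in the combination arm. The protocol claims no gut benefit from this, but it does not exclude one. A reader might infer that the combination can never win; the documents support only that a win is not expected on the stated mechanism.

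**The objective may be narrower.** The superiority aim is one introductory sentence, and the Discussion's question is answered by combination versus aspirin. That is fair, and the choice of pair may sit in an analysis plan that is not shown. But the two statements of the aim differ, and no analysis plan can make the wider one attainable against Xuesaitong. The title's noninferiority label does not settle it either, since the Introduction states superiority and no margin is given.

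**Planned attribution.** No text says that a fall in the Xuesaitong arm will be credited to Xuesaitong. This stands; it is a risk of misreading, not a stated plan.

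**Day-1 aspirin status.** A reader might infer that day 1 is certainly an on-aspirin baseline. The article describes no washout, but it is condensed and its flowchart is not shown. The conclusion does not need this: with a washout, the Xuesaitong arm would still be without aspirin to day 30.

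**Platelet aggregation.** A reader might also infer that near-zero changes within the single-drug arms would make active drugs look inert. The document does not support that. Section 2.10 compares groups, and under randomisation the between-arm difference in change equals the day-30 difference in expectation.

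**Conclusion.** The point holds for the gastrointestinal outcomes and is confined to comparisons with the Xuesaitong arm. On the protocol's own mechanism, the combination is not expected to show lower calprotectin than Xuesaitong alone: the expected difference is r(1-f)A, with zero as its most favourable value. The chance of a significant win is then 2.5% at best. Under incomplete protection with some recovery it is lower, and the combination may look significantly worse (17.1% to 89.9% in the half-protection cases shown). Xuesaitong versus aspirin cannot be read as a Xuesaitong effect.

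This rests on three assumptions: aspirin gives no calprotectin benefit of its own, the claimed mutual AUC rise adds none, and Xuesaitong removes the same share of aspirin injury in both arms. The percentages also rest on assumed values of A, f and r; the sign does not depend on those values. Combination versus aspirin remains a valid randomised test of protection, with 68.0% to over 99.9% power at complete protection for A from 0.3 to 0.8 SD and 131 per arm. It would be wrong to conclude that the calprotectin outcome as a whole is compromised.

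**What to change.** - Reconcile the Introduction with the Discussion by stating the gastrointestinal objective as combination superior to aspirin alone.
- Name combination versus aspirin as the confirmatory comparison for calprotectin, and as the deciding comparison for I-FABP and fecal occult blood.
- Describe the Xuesaitong arm, given criterion (6), as a switch from aspirin to Xuesaitong.
- Report that arm's gastrointestinal results as supportive, and state that its differences from the aspirin arm will not be attributed to Xuesaitong alone.

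This changes wording in the protocol and analysis plan only: no extra patients, visits or assays, and no change to treatment. The cost is giving up a gastrointestinal superiority claim over Xuesaitong alone, which the design is not expected to deliver. The platelet aggregation comparisons need no change on this account.

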#### 2.7.3. Drug Combination Group

Participants should take aspirin and Xuesaitong soft capsule on an empty stomach for 30 consecutive days. The interval between taking medicine is 30 minutes.

In all three groups, blood sampling will be carried out before administration on day 1 and after administration on day 30, and fecal samples will be collected on days 1 and 30.

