### 2.10. Data Management and Statistical Analysis Plan

We use EDC system to collect the data. The system administrator establishes the eCRF and conducts logic verification and range checks for data values. Two investigators fulfill double-data entry.

The analysis will be performed in a modified intention-treat population, which included all randomized participants who received at least one dose of Xuesaitong or aspirin. Continuous variables are presented as the mean ± SD and categorical variables as number and percentage. Comparisons between treatment groups were assessed using Student's *t*-test or Wilcoxon rank-sum test for continuous variables. Comparisons were assessed using the Fisher exact test for categorical variables. Data for patients who were lost to follow-up were censored at the time of the last contact. A multivariable Cox proportional-hazards regression analysis that included center and treatment as independent variables was conducted, and the results are expressed as hazard ratio (HR) with 95% confidence interval (CI). The incidence of adverse events was compared using the chi-squared test. *P* < 0.05 (two-sided) was considered to be statistically significant. All analyses were conducted using SPSS software 26.0.

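### Stool calprotectin above 50 µg/g is an entry criterion, but the schedule does not ensure that the result is available before randomisation and first dose

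*Protocol article*

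**What the plan says.** All references are to the protocol article.

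- **Entry rule.** Table 2, inclusion criterion (7): "Calprotectin in stool is above 50" µg/g.
- **Schedule.** Table 1 has a column headed "Screening D-7 to D1". The row that begins "Stool biomarkers (calprotectin; I-FABP" is empty in that column and marked at D1 and D30 only.
- **Text.** Section 2.1 says "fecal samples will be collected on days 1 and 30". The closing paragraph of section 2.7.3 repeats this for all three groups.
- **Start of treatment.** Section 2.1 says "Blood samples will be acquired 30 min before administration on day 1", so dosing begins on day 1. It adds "All treatment courses will last for 30 days".
- **Role of the marker.** Table 4 lists the change in calprotectin, measured by ELISA, as the primary outcome for reducing gastrointestinal side effects.
- **Analysis set.** Section 2.10 analyses "all randomized participants who received at least one dose of Xuesaitong or aspirin".

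**The concern.** A criterion that decides entry must be read before a participant is allocated. Here the test that decides it is not scheduled at screening, and its first scheduled sample falls on the day treatment starts. If the result comes back after allocation, the trial has to do one of two things with a participant at or below 50 µg/g.

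- **Keep the participant.** The analysis set in section 2.10 points this way. Randomisation stays intact, but the set then contains people outside the population that criterion (7) was meant to define, and the between-arm difference in calprotectin may be diluted.
- **Remove the participant.** This is an exclusion after allocation in an open-label trial. It departs from the stated analysis set and can bias the comparison if removals are handled differently between arms.

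The outcome at stake is one of the two primary outcomes, and the only primary outcome that addresses gastrointestinal injury.

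**Working it through.** There is no stated figure to reproduce, and the contradiction does not depend on arithmetic. The check sets the passages side by side.

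1. **What entry needs.** A stool calprotectin value above 50 µg/g (Table 2, criterion 7).
2. **What screening provides.** Table 1 marks stool routine at screening, within the routine laboratory row. Calprotectin is in a different row, with no screening mark. A stool specimen is therefore planned at screening, but no calprotectin assay on it.
3. **Whether another rule covers it.** Footnote 1 of Table 1 excludes people for clinically significant abnormalities found up to baseline. It is attached to the routine laboratory row, not to the calprotectin row.
4. **When calprotectin is first sampled.** On day 1, by Table 1 and by sections 2.1 and 2.7.3. These agree, so the blank cell is not an isolated slip in the table.
5. **When treatment starts.** On day 1, because the first blood draw is timed at 30 minutes before that day's administration.
6. **Order within day 1.** Only the blood draw is fixed relative to the dose. The stool sample has a day but no time, so it is not stated to be pre-dose.
7. **Whether allocation waits.** No section mentions an earlier clinical value, a same-day reading, or a hold on randomisation or dosing until the ELISA is read.

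The timeline as written is: screening (D-7 to D1) without calprotectin; D1, first calprotectin sample and first dose; D30, second calprotectin sample.

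**Dilution, in general form.** Let p be the share of treated participants at or below 50 µg/g, and let r be their between-arm effect as a fraction of the effect in eligible participants. The effect in the full set is then (1 − p) + p·r = 1 − p(1 − r) times the effect in eligible participants. With r between 0 and 1, this runs from 1 (no dilution, when p = 0 or r = 1) down to 1 − p (when r = 0). The article gives neither p nor r, so the loss cannot be put as a number.

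**Regression to the mean.** If the D1 value served as both entry test and baseline, selection above a cut-off would favour values that are high by chance. Calprotectin would then be expected to fall by D30 in every arm without any drug effect. Because all arms are selected by the same rule and then randomised, that expected fall is the same in each arm and cancels in the between-arm difference. It does not cancel in a within-arm change.

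**The case against.** The strongest reply is that this is a schedule slip in a condensed article. Four parts of it deserve a fair hearing.

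- **The screening window includes D1.** A day-1 stool assayed before allocation, or a recent clinical value, is conceivable. This stands against the inference that eligibility can never be known before treatment; the article does not support going that far. It does not remove the point, because the article provides for neither route.
- **A screening stool is planned.** Stool routine is marked at screening and at D31, so the sentence about days 1 and 30 cannot list every stool collection. This stands: a reader might infer that no stool is obtained before randomisation, and Table 1 shows otherwise. What is missing is the calprotectin assay, not the specimen.
- **Table 1 is not a full list of eligibility checks, and Figure 1 is not shown.** The diagnoses of CHD, angina and blood stasis have no named row either, and the screening step may be given in the figure or in a fuller protocol. That cannot be settled here. Calprotectin differs, however, in having its own row with its sampling days stated, and those days do not fit the criterion.
- **The planned comparisons are between groups.** Section 2.10 compares treatment arms and plans no within-arm test. A reader might infer that regression to the mean biases the trial's main result. The article does not support that: the effect is expected to cancel between randomised arms, and it arises only if the D1 value is actually used for selection.

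It is also tempting to say that participants at or below 50 µg/g have nothing to improve, so that r = 0. The article gives 50 µg/g only as an entry cut-off and says nothing about response below it.

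**Conclusion.** The point holds in a limited form. Table 2 makes calprotectin a condition of entry, while Table 1 and sections 2.1 and 2.7.3 schedule it first on the first dosing day, with no stated order relative to the dose. Followed as written, nothing ensures that the result is in hand before randomisation and first dose.

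The consequence is either possible dilution of a primary outcome or exclusion after open-label allocation. Which of these would occur, and how large it would be, is unknown: the share of candidates at or below the cut-off, their response, the ELISA turnaround and the time of randomisation on day 1 are not given. Confidence is high in the mismatch itself and lower in its consequences. It should be corrected because it touches eligibility and a primary outcome and is easy to repair.

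**What to change.** Reconcile Tables 1 and 2:

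1. Mark calprotectin in the screening column of Table 1. It can be run on the stool already planned there for stool routine.
2. State that the calprotectin result must be available before randomisation.
3. State in sections 2.1 and 2.7.3 that the D1 stool is collected before the first dose and serves as the baseline, separate from the screening value.
4. Base conclusions on calprotectin on between-arm comparisons adjusted for the D1 baseline, and draw no conclusion about protection from within-arm change.

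**Cost.** One calprotectin ELISA per screened person: 480 for the planned randomised participants (480 × 1), plus one for each person who fails screening. No extra stool collection is needed, and no dose, treatment rule or sample size changes.
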